## Assignment of interventions: blinding

### Who will be blinded {24a}

Since the interventions are performed by the participants, they are visible to them. Therefore, it is not possible to blind participants to the intervention. However, participants in the intervention groups are not told which intervention is being studied and which is the comparison. It is not possible to blind participants in the control group. The observer performing the measurements assigns participants to groups using sealed envelopes after the baseline measurements and is therefore blinded to group assignment at baseline but is not blinded to group assignment at post-measurement and follow-up. In this way, participants are also blinded and uninfluenced by the group assignment at baseline, and possible biases or expectations will not affect the results. The principal investigator who analyzes the data is blinded to group allocation throughout the study.

### How will be blinding be achieved {24b}

The blinded principal investigator is unaware of the group allocation of participants because the envelopes are sealed and inaccessible to him.

### Procedure for unblinding if needed {24c}

Not applicable; the participants in the study are not blinded with regard to their intervention.

## Data collection and management

### Plans for assessment and collection of outcomes {25a}

A detailed description of the outcome assessments and measurement instruments, including information on reliability, validity, SEM, and MDC, is provided in the outcome section. All assessments and measurements were trained by the assessor prior to conducting the study until full proficiency was achieved. The German versions of the CAIT and the FAAM are completed by the participants using prepared paper sheets [34, 41]. The results are then converted into prepared Word documents by the assessor. The YBT and MBESS scores are documented by the assessor immediately after the measurement using a priori constructed Word documents. Criteria for discontinuing or modifying allocated interventions are already mentioned in item 15a, and strategies for promoting participant adherence to each intervention are already mentioned in item 15c.

### Plans to promote participant retention and complete follow-up {25b}

In order to motivate participants during the 6-week study period, a participant fee of €20 will be paid after the post-examination. Furthermore, all participants will be provided with a comparison of their results, accompanied by explanatory notes, upon completion of the 12-week follow-up. The control group will receive the training plans for both groups after completing the 12-week follow-up.

### Data management {26}

Participants’ demographic and injury-related data are collected using a self-administered questionnaire. CAIT and FAAM data are documented using predesigned paper sheets. YBT and MBESS scores are documented by the assessor immediately after each measurement using a predesigned electronic Word document. Data are later exported to Excel files (Microsoft Excel Professional Plus 2019, Redmond, USA) for further processing. Gait analysis data from the respective measurement software are exported individually into Excel files (Microsoft Excel Professional Plus 2019, Redmond, USA) immediately after data collection. All relevant data are also transferred to a prepared Excel master spreadsheet for further analysis. All data are stored on a password-protected computer and on a secure server within the university computer system. In addition, data are stored on a password-protected external hard drive. Printed paper forms are kept in separate files for 10 years after the study is closed. Only study staff have access to the study files and the folders in which the database is stored. All data are checked before being transferred to the statistical software for inferential analysis (IBM SPSS Statistics for Windows, version 29.0.2.0 Armonk, NY: IBM Corp). Data integrity is ensured by referential data and range checks by two separate therapists. An individual privacy policy regarding disclosure/data collection, data management, data labeling, and data protection is included in the ethics approval.

### Confidentiality {33}

Before, during, and after the study, data are pseudonymized with a unique identification number for each participant and stored in folders accessible only to study team members to ensure confidentiality. Any records that contain names or other personal identifying information are kept separately from those used to record the study. The computers used and the external hard drive are password-protected, and only study team members have access to them. The data is stored on the university’s server, to which only members of the study team have access.

## Statistical methods

### Statistical methods for primary and secondary outcomes {27a}

Primary and secondary outcome measures are reported descriptively using mean ± SD or median and interquartile range according to their type (e.g., ordinal or interval scale). After testing the data for normal distribution using the Shapiro-Wilk test and histograms, for the primary outcomes of dynamic balance (YBT) and postural stability (MBESS), the significance of differences in post-intervention change within and between groups will likely be analyzed using repeated measures analysis of variance (ANOVA) (YBT) or Friedman tests or Kruskal-Wallis tests (MBESS) and post hoc tests with Bonferroni correction to account for multiple testing. After testing the data for normal distribution using the Shapiro-Wilk test and histograms, for the secondary outcome of gait biomechanics, the significance of differences in post-intervention change within and between groups will likely be analyzed using repeated measures analysis of variance (ANOVA) and post hoc tests with Bonferroni correction to account for multiple testing. For the secondary outcome of joint function (FAAM), the significance of differences in post-intervention change within and between groups will be analyzed using Friedman tests or Kruskal-Wallis tests and post hoc tests with Bonferroni correction to account for multiple testing. The global significance level is set to *α* = 0.05. No additional analyses are planned.

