### Outcomes {16}

#### Primary outcome measurements

##### Y-Balance Test

The Y-Balance Test (YBT) is a test of dynamic balance and is administered using a standardized test kit [25, 26]. In this study, the participant stands barefoot with the test leg on the stance platform of the test kit with the most distal portion of the big toe at the starting line. The hands are placed on the left and right iliac crest. The participant is instructed to move the target (reach indicator) with the free leg along the pipe as far as possible in the anterior, posteromedial, and posterolateral directions and to hold the end position for 3 s. Six trials are performed in each direction [27]. The first 3 trials are used to familiarize the participant with the task. The following 3 trials are recorded from the tape measure (5 mm increments) of each pipe at the edge of the reach indicator, at the point where the most distal point of the foot reaches, and used for further analysis. The participant is instructed to maintain balance during the trials and to return to the starting position after each trial. A trial is considered invalid and will be repeated if the participant touches the ground with the free leg, slips with the standing foot, falls off the stance platform, loses contact with the reach indicator while moving it to the maximum reach position, kicks the reach indicator forward, places the foot on the top of the reach indicator, or fails to return to the starting position under control. The maximum number of attempts is 3. The left leg is measured first. In addition, leg length is measured from the anterior superior iliac spine to the medial malleolus with the participant in the supine position to normalize anterior, posteromedial, and posterolateral reach distances to leg length. The following formula is used for normalization: reach distance/leg length × 100. The means of these normalized values are then calculated. In addition, the composite score is calculated using the following formula: (sum of the 3 reach distances)/3 times leg length × 100. In this study, the results are presented using the composite score. The minimum detectable change in YBT is between 7.7 and 14% [28]. The difference in change between the groups is assessed and calculated using parametric statistical analysis. The aggregation method is mean ± SD, and the measurements are taken before and after the 6-week intervention.

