##### Modified Balance Error Scoring System

In this study, the Modified Balance Error Scoring System (MBESS), which measures static balance, is performed on a foam surface (Balance Pad, ARTZT vitality®, Ludwig ARTZT GmbH, Dornburg, Germany) [29]. To perform the test, the participant stands in three positions on the balance pad with hands on the left and right iliac crest, eyes closed, and attempts to maintain the position for 20 s. Balancing in each of the three stance positions is scored out of a maximum of 10 points each. Errors are subtracted from the score, resulting in a maximum total MBESS score of 30 [30]. Errors are scored if the eyes are opened, the hands are removed from the pelvis, a step, trip, or fall occurs, hip abduction or flexion exceeds 30°, or the forefoot or heel is lifted. If the participant can hold the position for less than 5 s, the position is penalized with ten penalty points [31]. Reliability of the MBESS is moderate to strong with coefficients ranging from r = 0.6–0.88 [30]. The difference in change between groups is assessed and calculated using nonparametric statistical analysis. The aggregation method is median and interquartile range, and measurements are taken before and after the 6-week intervention.

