### Sample size {19}

An a priori sample size estimation based on the results of pilot measurements [40] examining change in dynamic balance after 6 weeks of balance training using the Mini Stability Trainer indicated that 33 participants (11 per group) would be needed to detect a mean difference of 4.6% in the composite score of the YBT with an effect size of *f* = 0.33 and a probability of 1 − *β* = 0.9 at a significance level of *α* = 0.05. To account for potential dropouts and loss to follow-up, the target number of participants is 36 (12 per group).

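### The primary Y-Balance analysis is left open until a normality pre-test has been read, against the unconditional parametric comparison stated with the outcome; MBESS falls under the same pre-test

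*Protocol article*

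**What the plan says.** Two parts of the protocol article describe the analysis of the two primary outcomes.

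- **Outcomes {16}, Y-Balance Test:** "The difference in change between the groups is assessed and calculated using parametric statistical analysis". No condition is attached.
- **Outcomes {16}, Modified Balance Error Scoring System:** "The difference in change between groups is assessed and calculated using nonparametric statistical analysis". Again there is no condition.
- **Statistical methods {27a}:** the choice for both outcomes comes "After testing the data for normal distribution using the Shapiro-Wilk test and histograms". The change within and between groups "will likely be analyzed using repeated measures analysis of variance (ANOVA) (YBT) or Friedman tests or Kruskal-Wallis tests (MBESS"), followed by Bonferroni-corrected post hoc tests.

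The hedge is not the section's general style. For FAAM, {27a} names the tests with neither a normality check nor the word likely.

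Section {27d} excludes additional analyses and gives adjusted analyses as an example. Under Sample size {19}, "the target number of participants is 36 (12 per group").

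**The concern.** A reader of the outcome section would take the YBT analysis as settled, and a reader of {27a} would take it as provisional. For a primary outcome this matters, because the analysis should not depend on how the trial's own data look. {27a} names no alternative for YBT should normality be doubted, so that branch is open rather than defined.

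MBESS has a milder form of the same conflict: it is already declared nonparametric, so a normality test has nothing to decide. Naming Friedman or Kruskal-Wallis also leaves unclear which test carries the comparison of arms. Friedman works within participants over time and cannot compare three parallel groups.

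A normality test on 12 values per arm is also weak evidence on which to choose. Repeated measures ANOVA needs approximately normal errors, and {27a} speaks only of testing the data.

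**Working it through.** **Inputs from the protocol.** Three arms at 1:1:1, 12 per arm (11 before the dropout allowance), YBT measured at two time points, f = 0.33, power 0.90, alpha 0.05. **Assumed, because not stated:** pre-test level 0.05; pre-post correlation rho; which values are tested; and that any single rejection counts.

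**1. The plan's own figure.** The sample size section states that the pilot data "indicated that 33 participants (11 per group) would be needed to detect a mean difference of 4.6% in the composite score of the YBT". For the group-by-time interaction, lambda = f² × N × m / (1 − rho), with m = 2 time points and df = 2 and N − 3.
- N = 33, rho = 0.5: lambda = 0.1089 × 33 × 2 / 0.5 = 14.37, power 0.9075.
- N = 36, rho = 0.5: lambda = 15.68, power 0.933.

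The stated 33 is reproduced, so the sizing matches a parametric comparison of change. It depends on rho: the same formula needs N = 45 at rho = 0.3 and N = 21 at rho = 0.7.

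**2. False alarms of the pre-test on truly normal data.**

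| What is tested | Formula | Simulated, n = 12 |
|---|---|---|
| Pooled residuals, one test | 5% | 4.6–5.5% |
| Change scores, three arms | 1 − 0.95³ = 14.3% | 13.4–14.1% |
| Six arm-by-time cells | 1 − 0.95⁶ = 26.5% | 25.3–26.0% |

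**3. Detection of real non-normality by one test at n = 12.** t with 5 df 12%; chi-square with 4 df 29%; lognormal (sigma 0.5) 30%; exponential 54%. Moderate skew is missed about 70% of the time.

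**4. Consequence of a mechanical switch.** Assumed rule: ANOVA on change, replaced by Kruskal-Wallis on change if any arm rejects; 12 per arm.
- Normal data, no effect: type I error 0.054 for the two-stage procedure, 0.053 for ANOVA.
- Normal data, effect as sized: power 0.932 two-stage, 0.934 ANOVA, 0.919 Kruskal-Wallis throughout.
- Exponential data, no effect: 0.053 two-stage, 0.040 ANOVA, although the switch occurs in 90% of trials.

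**5. Efficiency of the model.** With two time points and an outcome SD of 1 at each, the interaction test is a one-way ANOVA on change, with error variance 2(1 − rho). A linear model of the 6-week value with baseline as covariate has error variance 1 − rho². The ratio is 2/(1 + rho), which exceeds 1 for any rho below 1.

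Take an effect of 0.8 SD in both training arms and none in control. The between-arm sum of squares is 12 × (0.5333² + 2 × 0.2667²) = 5.12.

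| rho | Lambda, change | Lambda, adjusted | Power, change | Power, adjusted |
|---|---|---|---|---|
| 0.5 | 5.12 / 1.00 = 5.12 | 5.12 / 0.75 = 6.83 | 0.48 | 0.59 |
| 0.7 | 5.12 / 0.60 = 8.53 | 5.12 / 0.51 = 10.04 | 0.69–0.70 | 0.76 |

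The powers are simulated at 12 per arm; type I error was near 5% for both models.

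**The case against.** The best case for the plan is that little would go wrong in practice, and much of that case stands.

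- **No switch for YBT is written.** A reader might infer that a failed pre-test moves YBT to Friedman or Kruskal-Wallis. The sentence in {27a} labels the rank tests with MBESS, so the protocol does not say this.
- **The pre-test need not fire often.** A reader might take 26% as the protocol's own risk. It requires six separate tests, a 5% level and a rule that any rejection counts. None of these is stated, and the test is read together with histograms. With one pooled test the figure is about 5%.
- **The question would not change.** A reader might infer that a rank test abandons the arm-by-time effect. With two time points, Kruskal-Wallis on change is the rank counterpart of the interaction test. Friedman can serve the within-group part of what {27a} announces. The objection to Friedman holds only for comparing arms.
- **Error rates are barely disturbed.** Step 4 of the working shows this, and a seldom-rejecting pre-test mostly leaves ANOVA in place, as the outcome section says.
- **Detail may sit in an analysis plan that is not shown.** The missing pre-test level, unit and decision rule are therefore not counted as defects.
- **The adjusted model is a change of plan.** It departs from the named repeated measures ANOVA and from {27d}, and the sample size reproduces under the planned model.

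None of this removes the conflict: the same document states the YBT analysis once as fixed and once as likely and conditional.

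**Conclusion.** The point holds as one of internal conflict and pre-specification. {27a} leaves the primary YBT analysis open until the data are seen, against the outcome section. It also puts MBESS under a pre-test that its own nonparametric designation makes pointless, with one listed test that cannot compare arms.

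The documents do not support a claim of material error-rate inflation. Under the assumed mechanical rule the difference is 0.054 versus 0.053. The Shapiro-Wilk figures show only that the test is a poor selector at 12 per arm, and the false-alarm range of 5% to 26% rests on the stated assumptions.

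The efficiency gain is a separate benefit of settling the model now: 0.59 versus 0.48 at rho = 0.5, and 0.76 versus about 0.70 at rho = 0.7. These powers assume the 0.8 SD effect and normal data; the protocol gives no pre-post correlation.

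**What to change.** 1. In {27a}, remove the normality test as a selector of the primary tests, and delete the word likely.
2. Fix the YBT primary analysis as a linear model of the 6-week composite score on arm, with the baseline composite as covariate. Align the Y-Balance Test section, which stays parametric.
3. Amend {27d}, so that its exclusion of adjusted analyses no longer contradicts the primary model.
4. Use residual plots descriptively only. Name one rank-based or permutation version of the YBT comparison as a sensitivity analysis, reported whatever the plots show.
5. Fix Kruskal-Wallis on change as the between-arm MBESS test, in line with the MBESS section. If Friedman is kept, confine it to within-group description.

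The cost is a protocol amendment, reported to the ethics committee and the registry as {31} provides. It needs no new data or measurements and no more participants, but item 2 does replace the named primary model and is more than a wording change. It should be dated before anyone examines outcome data by arm; the protocol expects recruitment to end by January 2026. If the team prefers to keep repeated measures ANOVA, stating it without condition would resolve the YBT conflict but forgo the gain in power.

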### Objectives {10}

The study will be guided by the following specific objective: To determine whether the outcomes of dynamic balance, postural stability, gait biomechanics, and joint function improve in the intervention group and the balance training group after a 6-week intervention period and whether there is a significant difference compared to the control group.

The study is also based on the following hypotheses:The intervention group and the balance training group will lead to similar significant improvements in outcomes compared to the control group.It is also hypothesized that there will be no significant differences between the intervention group and the balance training group.

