#### Secondary outcome measurements

##### Function of the ankle joint

The German version of the Foot and Ankle Ability Measure (FAAM) questionnaire is a validated patient-reported outcome measure to identify functional limitations in individuals with CAI [32–34]. Twenty-one items relate to the Activities of Daily Living (ADL) subscale (FAAM-ADL) and eight items relate to the Sport subscale (FAAM-Sport) [35]. For each item, the possible responses range from 0 “no problems” to 4 “unable to do anything.” The score for each item in each subscale is summed (maximum score for the ADL subscale = 84; maximum score for the Sport subscale = 32). The sum is divided by the maximum score and then multiplied by 100. A resulting maximum score of 100 represents no functional limitation in each subscale. In patients with chronic ankle instability, FAAM-ADL and FAAM-Sport scores of <90 and <80, respectively, are considered to represent functional disability. The questionnaire is also suitable for recording changes over time. The minimum detectable change (MDC) is ±5.7 points for the ADL subscale and ±12.3 points for the Sport subscale [35]. The difference in change between groups is assessed and calculated using nonparametric statistical analysis. The aggregation method is median and interquartile range, and measurements are taken before and after the 6-week intervention, as well as at the 4- and 12-week follow-ups.

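### MBESS and FAAM: the plan offers Friedman or Kruskal-Wallis without fixing which decides between groups; Friedman cannot, and Kruskal-Wallis on change leaves the baseline unadjusted

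*Protocol article*

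**What the plan says.** All references are to the protocol article.

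- **Statistical methods {27a}, primary outcomes.** The sentence opens "the significance of differences in post-intervention change within and between groups will likely be analyzed using repeated measures analysis of variance (ANOVA) (YBT" and continues, for MBESS, with "Friedman tests or Kruskal-Wallis tests (MBESS) and post hoc tests with Bonferroni correction to account for multiple testing".
- **Statistical methods {27a}, FAAM.** The contrasts, both inside each arm and across arms, "will be analyzed using Friedman tests or Kruskal-Wallis tests and post hoc tests with Bonferroni correction to account for multiple testing".
- **Outcomes {16}, MBESS.** "The difference in change between groups is assessed and calculated using nonparametric statistical analysis". Two occasions are planned: "The aggregation method is median and interquartile range, and measurements are taken before and after the 6-week intervention".
- **Outcomes {16}, function of the ankle joint (FAAM).** The same between-group contrast is stated, with four occasions: "measurements are taken before and after the 6-week intervention, as well as at the 4- and 12-week follow-ups".
- **Additional analyses {27d}.** Adjusted analyses are listed among those not planned.
- **Sample size {19}.** The calculation covers the YBT composite only. No power is given for MBESS or FAAM.

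**The concern.** Friedman and Kruskal-Wallis are not substitutes. Friedman ranks the occasions within each participant and asks whether the occasions differ; group membership does not enter. Kruskal-Wallis ranks participants and asks whether groups differ. Joined by "or", with the primary-outcome sentence further softened to a likely analysis, the text leaves open which result settles a primary outcome.

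Two things are at stake. First, one of the two named options cannot answer the question that the outcome section sets for MBESS and FAAM. Second, the option that can answer it, Kruskal-Wallis on change, subtracts the baseline but does not adjust for it. With 36 participants, and a calculation that sized the trial for YBT alone, the power given up on MBESS may be material.

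**Working it through.** **1. The plan's own figure.** Inputs from {19}: f = 0.33, α = 0.05, power 0.90, three groups, N = 33. For a group-by-time interaction with m = 2 occasions, λ = f²·N·m/(1 − ρ). The article gives no ρ; with ρ = 0.5 assumed, λ = 0.1089 × 33 × 2 / 0.5 = 14.37 on 2 and 30 df. Power is 0.9075, and 33 is the smallest multiple of three that reaches 0.90. The figure reproduces as a group-by-time test on YBT. It says nothing about MBESS.

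**2. Friedman with two occasions.** Each participant contributes ranks (1, 2), (2, 1) or a tie, so only the direction of change survives. The statistic reduces to (n₊ − n₋)²/(n₊ + n₋), which is the sign-test chi-square. In three test data sets with ties the two statistics were equal: 1.333, 0.400 and 0.818. No group term appears. The reduction holds for MBESS (two occasions) but not for FAAM (four).

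**3. Kruskal-Wallis on change.** With two occasions, a between-group test on change is the group-by-time test: in a test data set the interaction F and the one-way F on change were both 8.414. Kruskal-Wallis on change is its rank counterpart. Its simulated type I error was 0.044 to 0.046. At the planned YBT effect, with normal change and ρ = 0.5, its power was about 0.89 at 11 per group and 0.92 at 12, some 2 to 3 points below ANOVA on change. It is valid and close to its parametric equivalent.

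**4. What leaving the baseline unadjusted costs.** For a score with SD σ at both occasions:

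- variance of change = 2σ²(1 − ρ)
- variance of the final score adjusted for baseline = σ²(1 − ρ²)
- ratio, adjusted to change = (1 + ρ)/2

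The ratio is 0.65, 0.75, 0.85 and 0.925 at ρ = 0.3, 0.5, 0.7 and 0.85. Adjustment therefore helps most when ρ is low.

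Simulation on an MBESS-like score: 12 per arm; rounded scores bounded at 0 and 30; mean 18 and SD 4 (both assumed); gain of 0.8 SD (0.8 × 4 = 3.2 points) in both training arms and none in control. Rank ANCOVA regresses the rank of the 6-week score on group and the rank of baseline.

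| ρ (assumed) | Kruskal-Wallis on change | Rank ANCOVA | Difference |
|---|---|---|---|
| 0.3 | 0.33 | 0.47 | +0.14 |
| 0.5 | 0.43 | 0.55 | +0.12 |
| 0.7 | 0.66 | 0.72 | +0.06 |
| 0.85 | 0.93 | 0.92 | −0.01 |

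Type I error of rank ANCOVA was 0.047 to 0.054. A separate run of 3,000 trials gave 0.32 against 0.49, 0.45 against 0.54, and 0.66 against 0.71 at ρ = 0.3, 0.5 and 0.7, the same pattern.

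**The case against.** The strongest reply is that the text already has a sensible reading. {27a} speaks of change within and between groups, so Friedman serves the first and Kruskal-Wallis the second, and the outcome section asks for the difference in change between groups. On that reading the between-group test is valid, the rest is detail for an analysis plan that is not shown, and rank ANCOVA is a preference that {27d} excludes. Much of this stands: Kruskal-Wallis on change is a sound test, and naming it outright would be an acceptable minimum. What does not stand is that the choice was merely left open. The article names the two tests as alternatives for a primary outcome, and one of them cannot do the job. {27d} shows only that baseline adjustment needs a matching edit there.

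Three stronger readings are tempting, and the documents do not support them.

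- **That the plan contains no group-by-time test.** For MBESS it does, if Kruskal-Wallis is applied to change (step 3). For FAAM neither test gives one overall interaction test, but Kruskal-Wallis on change at a given visit still compares the arms.
- **That the sign-test weakness extends to FAAM.** It does not, because FAAM has four occasions.
- **That training effects will be claimed because training arms reach significance and control does not.** The objective does ask whether outcomes "improve in the intervention group and the balance training group after a 6-week intervention period", but the same sentence goes on to ask about the difference from control, and both hypotheses are between-group. With an equal true change of 0.5 SD in all arms and 12 per arm, Friedman is significant in one arm with probability 0.233. At least one training arm but not control is then significant with probability (1 − 0.767²) × 0.767 = 0.32. If the Bonferroni correction were spread over the three arms (an assumption about its scope), this falls to 0.135. Either figure describes an inference that the plan does not state. It is a reason to rule that inference out in words, not evidence that it is intended.

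**Conclusion.** The point holds in limited form. {27a} does not fix the test that decides the between-group question for MBESS and FAAM, and one of its two candidates has no group term and, for MBESS, uses only the direction of change. The other candidate is valid but gives up about 12 to 14 points of power at correlations of 0.3 to 0.5, 6 points at 0.7, and none at about 0.85, compared with a rank analysis adjusted for baseline.

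These sizes rest on an assumed mean, SD, gain and correlation, none of which the article gives for MBESS; no such figures were simulated for FAAM. That Friedman cannot test a group difference, and is a sign test with two occasions, rests on no assumption. The matter should be settled before the data are analysed. It does not undermine the design.

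**What to change.** In {27a}:

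1. For MBESS, name one between-group test: rank ANCOVA, with the rank of the 6-week score regressed on group and the rank of baseline, and Bonferroni-corrected pairwise contrasts.
2. Use the same test for FAAM-ADL and FAAM-Sport, with the 6-week score as the main time point and the 4- and 12-week follow-ups as supportive.
3. Remove Friedman as a deciding test for MBESS. Report within-arm change as median and interquartile range, and state that within-arm p-values support no claim of effect.

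In {27d}, amend the exclusion of adjusted analyses so that it does not conflict with the baseline covariate.

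Cost: a wording change, no new data, and one error degree of freedom (32 instead of 33 with 36 participants). There is no gain in power if the pre-post correlation turns out to be about 0.85 or higher. If the sponsor prefers not to adjust, the minimum is to state that Kruskal-Wallis on change from baseline is the between-group test, at a named visit for FAAM, and that Friedman is within-arm and supportive only.
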